### Data analysis

#### Primary analyses

We aim to test the hypothesis that simple home-based impairment-targeted exercises can improve those impairments in older adults with knee pain. To this end, all those participants receiving the exercise programme for a given impairment will have raw changes calculated for the measure of that impairment over the 12 weeks of the study. Mean differences in the change values (or their non-parametric equivalents, depending on the distribution of the change values) will then be calculated for each of the three impairment groups. Finally, in each instance, the mean differences in the change values for participants receiving an exercise programme targeted at a given impairment will be compared with those of participants not receiving an exercise programme targeted at that particular impairment, using the independent-samples t-test or its non-parametric equivalent.

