**Methods/Design:**

We aim to recruit 60 participants from an existing observational cohort of community-dwelling older adults with knee pain. Participants will all have at least one of the three physical impairments of weak quadriceps, a reduced range of knee flexion and poor standing balance. Each participant will be asked to undertake a programme of exercises, targeted at their particular combination and degree of impairment(s), over the course of twelve weeks. The exercises will be taught and progressed by an experienced physiotherapist, with reference to a "menu" of agreed exercises for each of the impairments, over the course of six fortnightly home visits, alternating with six fortnightly telephone calls. Primary outcome measures will be isometric quadriceps strength, knee flexion range of motion, timed single-leg standing balance and the "Four Balance Test Scale" at 12 weeks. Key secondary outcome measures will be self-reported levels of pain, stiffness and difficulties with day-to-day functional tasks (WOMAC). Outcome measures will be taken at three time-points (baseline, six weeks and twelve weeks) by a study nurse blinded to the exercise status of the participants.

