### Outcome measures

All outcome measures will be administered by a study nurse entirely independently of the study physiotherapists. These measures will be taken at the first nurse home visit, following taking of written, informed consent, and again at the second and third nurse visits in weeks 6 and 12 of participants' involvement in the study. The outcome measures administered at all three time-points will be as follows:

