#### Sensitivity analyses

To explore the potential contribution of regression to the mean, data on the three impairment measures collected for our participants at the baseline, 3-year and 6-year clinical assessment study clinics [23] will be compared to the corresponding measures taken at the initial TargET-Knee-Pain study nurse visit.

To explore the contribution of potential ceiling effects (i.e. how much improvement can be possible in the comparison groups, who will inevitably be starting with higher measures for the given target impairments), a definition of "lack of impairment" for each of the three impairments will be derived, based on age-gender stratified norms. The percentage of individuals who lack each of the target impairments, according to these definitions, will be determined at 12-week follow-up, and will be compared between those who were and those who were not impaired in that measure at recruitment.

To explore the effects that poor adherence with the exercise programmes may have on the results, efficacy subgroup analyses will be conducted, whereby the analyses will be repeated in the subgroup of individuals deemed to have been adherent with the exercise programmes and compared with the subset deemed not to have been adherent. For this purpose, inadequate adherence will be defined as follows:

• Not having done any of the exercises at all in the course of at least one rolling calendar week throughout the 12 week period of their involvement in the study (according to the daily exercise diaries).

• Not having done any of the exercises at all on a cumulative total of 12 days throughout the 12 week period of their involvement in the study (according to the daily exercise diaries).

• Participant self-report of not having done their exercises as often as they were advised to in either the 6 or 12 week questionnaires.

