#### Secondary analyses

To investigate whether improvements in the target impairments are reflected in improvements in self-reported knee pain, stiffness and functional difficulties, mean changes (or their non-parametric equivalents, depending on the distribution of the change values) in the corresponding WOMAC subscale scores, between baseline and 12 weeks, will be calculated across all individuals, irrespective of which impairments they received exercises for. Associations between changes in the target impairments and changes in the WOMAC subscales will be examined by calculating Pearson's product-moment correlation coefficients (or their non-parametric equivalents, depending on the distribution of the change values).

To investigate whether improvements in self-report measures of pain, stiffness and physical function will be greater amongst those participants receiving exercises targeted at more than one impairment than amongst those participants receiving exercises targeted at only one impairment, mean differences in WOMAC change scores for the three subscales (or their non-parametric equivalents, depending on the distribution of the change values) will be calculated for both of these groups and compared across them.

To investigate the feasibility of this intervention and its acceptability to patients, responses to free-text and Likert-response-type questions will be analysed. This will include questions about barriers to adherence to the exercise programmes, and questions soliciting participants' views regarding participation in the study and the ways in which they believe that things could be improved. Analyses will include frequency counts of the various responses to Likert-type questions and a thematic analysis of free-text responses in the 12 week questionnaire.

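### The stated 12-week change analyses of impairments and WOMAC use only baseline and week 12, so without a further rule the week-6 values of participants lost later go unused

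*Protocol article*

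**What the plan says.** Under Outcome measures, the article has the nurse measure at the first home visit and "again at the second and third nurse visits in weeks 6 and 12 of participants' involvement in the study". The list that follows, introduced by "The outcome measures administered at all three time-points will be as follows", covers all four primary impairment measures and WOMAC.

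The analyses of change use two of those three visits:

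- Primary analyses: participants given the programme for an impairment "will have raw changes calculated for the measure of that impairment over the 12 weeks of the study". These changes are compared with those of participants not given that programme, "using the independent-samples t-test or its non-parametric equivalent".
- Secondary analyses: mean changes "in the corresponding WOMAC subscale scores, between baseline and 12 weeks, will be calculated across all individuals". Impairment changes are then correlated with WOMAC changes, and WOMAC change is compared between participants with one and with more than one targeted impairment.
- Sensitivity analyses: in the ceiling-effect check, the percentage without each impairment "will be determined at 12-week follow-up". The adherence check repeats the main analyses in subgroups.

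No stated analysis uses the week-6 impairment or WOMAC values. The article also states no rule for a missing week-12 value.

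**The concern.** A raw 12-week change does not exist for a participant without a week-12 measurement. A t-test on such changes therefore leaves out someone who attended the week-6 visit and then left, although that person's mid-course strength, flexion, balance and WOMAC are on file.

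This matters because the study has no control arm and its result is meant to inform whether the approach deserves a randomised trial. Loss related to response is plausible on the article's own account: the Interventions section expects temporary pain and stiffness from the exercises and devotes considerable effort to sustaining adherence. If participants who are not improving leave more often, the mean gain among completers is too favourable. Week-6 values are the only post-baseline impairment and WOMAC outcome data that could show this for participants lost between weeks 6 and 12.

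**Working it through.** **Which stated analyses need a week-12 value**

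| Analysis | Needs week 12? |
|---|---|
| Change in each impairment, targeted versus untargeted | Yes |
| WOMAC change, pooled and one versus more than one impairment | Yes |
| Correlation of impairment change with WOMAC change | Yes |
| Ceiling-effect percentages | Yes |
| Regression to the mean (cohort clinic data against first nurse visit) | No |
| Frequency counts of Likert items asked at week 6 | No |

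The dependence is confined to the outcome analyses, but these include all the main ones.

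**The article's own figure.** The Sample section gives about 86% power for 60 participants to detect 8° or 8 kg at a 5% error rate. It gives no SD, sidedness or group split, so 86% cannot be reproduced forward. The point here does not depend on it.

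**Possible bias in the within-group gain.** Inputs, both assumed because the documents give neither: w, the proportion without a week-12 value, and k, the leavers' true 12-week gain as a fraction of the completers' gain. The all-participant mean is the completer mean × [(1 − w) + wk], so

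overstatement = 1/[(1 − w) + wk] − 1.

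| w | k | (1 − w) + wk | Overstatement | True mean if completers show 8° |
|---|---|---|---|---|
| 0.10 | 0.5 | 0.95 | 5% | 7.6° |
| 0.10 | 0 | 0.90 | 11% | 7.2° |
| 0.20 | 0.5 | 0.90 | 11% | 7.2° |
| 0.20 | 0 | 0.80 | 25% | 6.4° |

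With k = 1 (loss unrelated to gain) the overstatement is zero. The formula covers the within-group gain only. In the targeted-versus-untargeted contrast the bias can go either way, depending on who leaves from each side.

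**Possible loss of precision.** Take the stated 86% as holding for 60 completers, two-sided, with proportional loss d across groups (assumed). Then power = Φ[(1.960 + 1.080)√(1 − d) − 1.960].

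- d = 0.10 (54 left): 3.040 × 0.949 − 1.960 = 0.924, power 82.2%.
- d = 0.20 (48 left): 3.040 × 0.894 − 1.960 = 0.759, power 77.6%.

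**What week 6 would recover.** This depends on how many participants leave after rather than before week 6, and on the correlation between the 6- and 12-week changes. The documents give neither, so no figure can be attached.

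**The case against.** The strongest reply is that the exclusion is inferred. The article names an outcome and a test; it neither prescribes complete cases nor rules out imputation. Missing-data rules are commonly left to a fuller document, so their absence from a journal article is no fault. Twelve weeks is also the declared primary time-point, and choosing it is not an error. All of that stands, which is why the point is conditional on no further rule existing. It does not remove the point, which concerns a method the article does state: a raw-change t-test cannot itself use week 6.

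Three stronger readings are tempting but unsupported.

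- A reader might infer that someone lost after week 6 disappears from every analysis. They do not. They stay in the regression-to-the-mean comparison and in counts of the week-6 adherence and global-change items, and the adherence definition draws on the 6-week questionnaire.
- A reader might take "between baseline and 12 weeks, will be calculated across all individuals" as a promise of complete follow-up that a change score then breaks. The sentence goes on to say that this is regardless of which impairments were treated, so it means pooling over impairment groups.
- A reader might take 5-25% as what the change would correct. It is the total completer bias under assumed loss and assumed poorer response.

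The objection that a mixed model does not suit every primary measure is also right. The Four Balance Test Scale is ordinal. Single-leg balance time is capped at 30 seconds, and its entry thresholds lie below 2 to 8 seconds, so skew is likely. The article's non-parametric fallback is sensible for these.

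**Conclusion.** The point holds in limited form. The stated analyses of 12-week change in impairments and WOMAC use baseline and week 12 only. Unless a rule outside the article provides otherwise, participants lost after week 6 do not contribute to them, although their week-6 values are collected. If those who leave improve less, the completer mean overstates the within-group gain. The documents cannot fix the size; 5-11% at 10% loss and 11-25% at 20% loss follow only if leavers gain between half and none of what completers gain. The documents do not show that such loss will occur. The change is still worth making, because the data will be in hand and the 12-week target is unchanged.

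**What to change.** For quadriceps strength and knee flexion, estimate the 12-week change and the targeted-versus-untargeted contrast from a repeated-measures mixed model with baseline, week 6 and week 12 as outcomes and visit, group and their interaction as terms. Do the same for the WOMAC subscales, using the article's own grouping there (one versus more than one targeted impairment), or visit alone for the pooled mean. With complete data this gives the same estimated contrast as the change scores. Keep the completer change-score t-test as a sensitivity analysis.

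Keep the planned non-parametric approach for the Four Balance Test Scale. Check model fit for the capped single-leg balance time, and revert to the non-parametric analysis if it fits poorly.

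No further data collection is needed. The costs are slightly more analysis work and reliance on data being missing at random given baseline and week-6 values, which is weaker than what the completer comparison assumes. Participants lost before week 6 still add no post-baseline information, and the correlation and ceiling-effect analyses remain limited to those with week-12 values.

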#### Sensitivity analyses

To explore the potential contribution of regression to the mean, data on the three impairment measures collected for our participants at the baseline, 3-year and 6-year clinical assessment study clinics [23] will be compared to the corresponding measures taken at the initial TargET-Knee-Pain study nurse visit.

To explore the contribution of potential ceiling effects (i.e. how much improvement can be possible in the comparison groups, who will inevitably be starting with higher measures for the given target impairments), a definition of "lack of impairment" for each of the three impairments will be derived, based on age-gender stratified norms. The percentage of individuals who lack each of the target impairments, according to these definitions, will be determined at 12-week follow-up, and will be compared between those who were and those who were not impaired in that measure at recruitment.

To explore the effects that poor adherence with the exercise programmes may have on the results, efficacy subgroup analyses will be conducted, whereby the analyses will be repeated in the subgroup of individuals deemed to have been adherent with the exercise programmes and compared with the subset deemed not to have been adherent. For this purpose, inadequate adherence will be defined as follows:

• Not having done any of the exercises at all in the course of at least one rolling calendar week throughout the 12 week period of their involvement in the study (according to the daily exercise diaries).

• Not having done any of the exercises at all on a cumulative total of 12 days throughout the 12 week period of their involvement in the study (according to the daily exercise diaries).

• Participant self-report of not having done their exercises as often as they were advised to in either the 6 or 12 week questionnaires.

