### Eligibility criteria

Potential participants in our study will be attendees at the CAS(K) 6-year-follow-up research assessment clinics, who are men and women, all aged 56+ years with a history of knee pain. To be included in this study, they will have measurements for at least one of the target impairments (quadriceps strength, degree of knee flexion and single-leg standing balance) that fall below the lowest quartile of age- and gender-stratified values recorded at the baseline assessments between 2002 and 2003 (Table 1). In order to be considered for inclusion in the study, individuals must be willing and able to commit to a programme of exercises for a 12-week period.

**Table 1 T1:** Age and gender thresholds for study inclusion

	Male	Female
Range of knee joint flexion		
55-64 years	< 128°	< 127°
65-74 years	< 125°	< 122°
75+ years	< 120°	< 117°
		
Isometric quadriceps strength (kilograms force)		
55-64 years	< 18.1	< 11.3
65-74 years	< 17.2	< 9.4
75+ years	< 13.9	< 9.0
		
Single-leg standing balance (seconds)		
55-64 years	< 8	< 5
65-74 years	< 3	< 3
75+ years	< 2	< 2

The exclusion criteria are: total knee replacement of either knee joint; an existing diagnosis of inflammatory arthropathy; lower limb weakness from neurological conditions; receiving medication that adversely affects standing balance; open wounds on the anterior aspect of either distal shin; a self-report of unstable angina or uncontrolled hypertension/hypotension; an inner ear problem that compromises standing balance; no mobile or home telephone; unavailability for fortnightly home visits or telephone contact for the whole of a given working week of their potential involvement in the study; an inability to transfer independently from lying to sitting or from sitting to standing; currently receiving physiotherapy for their knee problem.

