### Interventions

In each case the study intervention will last for 12 weeks. Three exercise packages have been developed with reference to published literature (one for each of the three target impairments): one for quadriceps strengthening, one for knee flexion stretches, and one for balance retraining. These exercise packages systematically progress each of the exercises through photographically-illustrated stages. Details of the packages are available as Additional files 1, 2 and 3. Participants will be assigned to receive one or more of these exercise packages, based on whether their measurements for either leg for the corresponding target impairments fall below the thresholds in Table 1. The exercises will be selected and the level-of-difficulty tailored to the abilities of the individual participant on the basis of the assessment by a study physiotherapist during the first physiotherapist home visit. This assessment will consist of a standardised clinical history taking and physical assessment, together with measurement of the target impairment(s). Selection and tailoring of the exercises will take the following factors into account:

• The presence and degree of the three impairment(s).

• The safety of the participant.

• Participant ease of performance when practising the exercises under the supervision of the physiotherapist.

• The preferences, motivations and concerns of the individual participant.

The dosage and frequency of the exercises will be decided by negotiation with the individual participant. The physiotherapist will also employ the following elements of advice and reassurance when teaching the exercises to the participants:

• Explicit identification of activities of daily living that could be improved by an improvement in the identified impairment(s).

• Education regarding the importance of strong quadriceps and/or good flexion range of motion and/or good balance both to the health of the knee joints and to overall function.

• Advice and reassurance regarding the expected adverse effects of the exercises, such as temporary pain and stiffness, including advice about the benign nature of these side-effects and the use of ice, heat and simple analgesia to manage them.

• Reassurance that the individual can contact one of the study physiotherapists by telephone at any time regarding any queries or concerns.

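### Impairment groups are formed by age- and gender-specific cut-offs, but the primary comparison pools raw change with no adjustment for age or gender

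*Protocol article*

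**What the plan says.** Under Eligibility criteria, a participant must have at least one impairment measure "fall below the lowest quartile of age- and gender-stratified values recorded at the baseline assessments between 2002 and 2003". Table 1 turns this into six cut-offs per measure, one for each combination of gender and age band (55-64, 65-74, 75+). Under Interventions, packages are assigned "based on whether their measurements for either leg for the corresponding target impairments fall below the thresholds in Table 1".

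Under Primary analyses, those given the package for an impairment "will have raw changes calculated for the measure of that impairment over the 12 weeks of the study", and these changes "will be compared with those of participants not receiving an exercise programme targeted at that particular impairment, using the independent-samples t-test" or a non-parametric counterpart. Neither age nor gender appears in that comparison.

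Under Sensitivity analyses, the ceiling-effect check describes the comparison groups as those "who will inevitably be starting with higher measures for the given target impairments". That check itself uses norms stratified by age and gender. It is the only place where age and gender enter the analysis.

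**The concern.** The variables that decide who counts as impaired are left out of the comparison between impaired and unimpaired. The study is uncontrolled, and all comparators for one impairment are in the study because they have another. The mix of men, women and age bands in the two groups is therefore left to whatever recruitment yields, separately for each of the three impairments.

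Quartile cut-offs set within strata tend to even out the mix, but they do not secure it. They come from the 2002-2003 assessments and are applied about six years later, and either leg is enough for assignment. If raw gains differ by gender or age, any difference in mix enters the estimated effect of targeting.

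A second, smaller matter is the word *inevitably* in the ceiling check. Table 1 ensures a higher start only against people in the same age-gender stratum, and only at screening.

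**Working it through.** **1. Inputs from Table 1** (ages 55-64, 65-74, 75+)
- Strength: men 18.1, 17.2, 13.9 kg; women 11.3, 9.4, 9.0 kg.
- Flexion: men 128, 125, 120 degrees; women 127, 122, 117 degrees.
- Balance: men 8, 3, 2 s; women 5, 3, 2 s.

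**2. How far the scales differ by gender**
- Strength ratios, men to women: 18.1/11.3 = 1.60; 17.2/9.4 = 1.83; 13.9/9.0 = 1.54.
- Gaps: strength 6.8, 7.8, 4.9 kg; flexion 1, 3, 3 degrees; balance 3, 0, 0 s.
- A gender difference in raw gain is therefore most plausible for strength.

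**3. Individuals in different strata.** A man aged 55-64 at 18.0 kg is targeted, while a woman aged 75+ at 9.0 kg is a comparator. In whole units the largest such overlaps are 18.0 − 9.0 = 9.0 kg, 127 − 117 = 10 degrees and 7 − 2 = 5 s. Six strata give 6 × 5 = 30 ordered pairs. Treating the measures as continuous, an impaired person in one stratum can start above an unimpaired person in another in 15 pairs for strength, 15 for flexion and 13 for balance.

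**4. Group means.** These were simulated for strength and flexion, but not for balance. All of the following are assumptions: 45% men; age bands 20/45/35%; half impaired; values normal within stratum with the lower quartile at the Table 1 cut-off; 60 participants per study; 3000 studies.
- Strength, coefficient of variation 25% to 45%: targeted mean 10.3 down to 7.9 kg, comparator mean 16.8 up to 21.6 kg.
- Flexion, SD 8 to 12 degrees: targeted 118 down to 115, comparator 131 up to 136 degrees.
- The group means reversed in none of the 3000 studies.
- With 80% of men and 20% of women impaired, strength means reversed in at most 0.6% of studies. Reversal reached 15% to 42% only with 90-95% of men and 5-10% of women impaired and a coefficient of variation of 25%.

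**5. Size of the confounding in strength change**

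Spurious difference = (difference in share of men) × (proportional gain) × (male-female gap in level).
- Assumed: a 20-point difference in share, a 10-20% gain in everyone, a 7-9 kg gap.
- Low: 0.2 × 0.1 × 7 = 0.14 kg. High: 0.2 × 0.2 × 9 = 0.36 kg.
- With the Table 1 cut-off gaps instead: 0.2 × 0.1 × 4.9 = 0.10 kg to 0.2 × 0.2 × 7.8 = 0.31 kg.
- Against the 8 kg in the Sample section: 0.10/8 = 1% to 0.36/8 = 4.5%.

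**6. Effect on precision.** The Sample section gives about 86% power but no SD, sidedness or group split, so the figure cannot be reproduced. Solving two-sided for the SD, SD = 8 / [(1.960 + 1.080) × √(1/n₁ + 1/n₂)], gives 10.2 for 30/30, 9.6 for 20/40 and 8.8 for 15/45. The gender gap in change from step 5 is 0.1 × 7 = 0.7 kg to 0.2 × 9 = 1.8 kg. With equal numbers of men and women this adds an SD of at most 1.8/2 = 0.9 kg. As a share of variance that is 0.81/10.2² = 0.8% to 0.81/8.8² = 1.0%, or 0.81/4² = 5% if the SD of change were only 4 kg (assumed).

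**The case against.** The strongest reply is that change already subtracts each person's own starting value, so a difference in level between men and women is not bias. Confounding needs two things together: a different age-gender mix in the two groups, and change that depends on age or gender. The protocol shows neither. Stratum-specific quartiles push the mix towards balance, and an imbalance that arises purely by chance is sampling error already carried in the standard error. All of this stands, and it is why the point is conditional and small. It does not remove the point, because the groups are formed by selection, not by randomisation, and an imbalance need not be due to chance.

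It can also be said that covariates are often left to an analysis plan in a proof-of-principle study. Here, however, the article names the primary test and the raw outcome, so the method is stated and can be improved.

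A reader might infer from step 3 that the statement about higher starting measures is false under Table 1, or that the ceiling check loses its premise. The documents do not support either. The sentence is about comparison groups, whose means ran in the stated direction under all plausible assumptions tried. The check is defined on age-gender norms, the scale on which the premise holds at screening. The only fault is that *inevitably* claims more than Table 1 secures.

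**Conclusion.** The point holds as a cheap improvement to a stated method. The primary comparison leaves out the two factors that define its groups, and the age-gender mix is uncontrolled. For strength the possible distortion is about 0.1 to 0.4 kg, which is small beside 8 kg. That range rests on the assumed imbalance, proportional gain and gender gap, and the first two have no source in the documents. No figure can be derived for flexion or balance. The loss of precision from pooling is also slight.

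It would go too far to conclude that the primary result will be biased: that depends on a difference in mix and on change varying by age or gender.

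On wording, a higher start is expected on average. It is secured only within a stratum and only at screening, taking package assignment to rest on the screening measurements, as the reference to impairment at recruitment in the ceiling check suggests. Change is counted from the later nurse home visit. The ceiling concern is unaffected.

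**What to change.** - In each primary between-group comparison, fit a linear model of 12-week change on targeted versus not targeted, with gender and Table 1 age band as covariates. Keep the unadjusted t-test or its non-parametric counterpart as a supportive analysis.
- In the ceiling-effect paragraph, replace "who will inevitably be starting with higher measures for the given target impairments" with: *who are expected on average to start with higher measures, and at screening are at or above their own age-gender threshold*.

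The cost is wording plus at most three degrees of freedom (one for gender, two for age band) in 60 participants. Age and gender are already needed to apply Table 1, so no new data are required.

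Two alternatives are not advised. A fully stratified comparison would have 60/(6 × 2) = 5 people per cell on average, which is too sparse. Expressing change relative to the person's own cut-off does nothing by subtraction, because the cut-off cancels. By division it is unstable for balance: a 1 s change is 1/2 = 50% at a 2 s cut-off but 1/8 = 12.5% at 8 s.

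The adjustment does not cure regression to the mean, which remains a separate matter. If the baseline value is ever added to address it, gender and age band should accompany it, because targeted and comparator participants with the same screening value come from different strata.

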#### Primary outcome measures - impairments

• Maximal isometric quadriceps strengths (continuous scale)

(measured in sitting at 90° knee flexion, using a Chatillon DFX-200 electronic dynamometer, stabilised against a wall, using a bespoke stabilisation rig (Additional file 4)).

• Degree of active end-range knee flexion (continuous scale).

(measured in supine on a portable examination couch, using a standard 10-inch universal perspex goniometer, with reference to the anatomical landmarks of the lateral malleolus of the ankle and the greater trochanter of the femur).

• The Four Balance Test Scale [27,28] (ordinal scale, range 0-5)

(tests the ability of the individual to balance in each of four postures for 10 seconds - feet together; semi-tandem stand; tandem stand and single leg stand).

• A modified version of Franchignoni et al's timed standing balance test [29,30] (continuous scale) (single-leg stance, hands on hips, up to a maximum of 30 seconds).

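### The ceiling-effect sensitivity analysis is strongly confounded by entry status and, unless its norm sits near the scale maximum, does not measure room to improve

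*Protocol article*

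**What the plan says.** Under Sensitivity analyses, the protocol article sets out to explore ceiling effects, which it explains as "how much improvement can be possible in the comparison groups, who will inevitably be starting with higher measures for the given target impairments". The method has three parts:

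- A definition of being unimpaired is to be derived for each measure from age-gender norms. The cut-off is not given and is not said to equal the Table 1 thresholds.
- The percentage meeting that definition "will be determined at 12-week follow-up".
- That percentage is "compared between those who were and those who were not impaired in that measure at recruitment".

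Impairment at recruitment means values that "fall below the lowest quartile of age- and gender-stratified values recorded at the baseline assessments between 2002 and 2003" (Eligibility criteria). Exercise packages are assigned "based on whether their measurements for either leg for the corresponding target impairments fall below the thresholds in Table 1" (Interventions), so for each measure the impaired group is also the group that receives the matching exercises. The result being checked is in Primary analyses: changes over 12 weeks in targeted participants are "compared with those of participants not receiving an exercise programme targeted at that particular impairment, using the independent-samples t-test" or a non-parametric equivalent.

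Two outcomes have a stated upper limit, both for balance: the timed test ("single-leg stance, hands on hips, up to a maximum of 30 seconds") and the Four Balance Test Scale, scored 0 to 5.

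**The concern.** The stated question is about headroom: could comparison participants have improved, and if not, how much of the difference in change scores comes from that? The planned statistic looks at 12-week status only. It counts nobody at or near a maximum at baseline, and it does not repeat the change-score comparison with such people set aside.

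What it does compare is a cut on a measure between groups already separated by a cut on that measure. A gap is therefore expected without any treatment effect or ceiling, and a reader could mistake it for evidence about ceilings.

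The primary comparison is exposed to this problem. Someone who holds single-leg stance for 30 seconds at baseline can only record a change of zero or less. If such people are mainly in the group not given balance exercises, that group's mean change is held down and the targeted group may look better on balance than it should. This is the only planned analysis aimed at that risk.

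**Working it through.** The article gives no figure for this analysis, so there is none to reproduce. Its power statement (60 participants, about 86%) does not bear on the point.

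**Inputs from the article.** Entry requires at least one of three measures below the lowest age-gender quartile. Groups are split on the index measure at recruitment. The endpoint is the share at or above a norm at 12 weeks. Table 1 balance thresholds run from 2 to 8 seconds; the timed test stops at 30 seconds.

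**Assumptions, not in the article.** Standardised normal measures; test-retest reliability r of 0.7, 0.8, 0.9 or 0.95; correlation between measures of 0 or 0.3; norm at the 25th or 50th percentile; exercise effect of 0 to 1.5 SD in the impaired group only.

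**Step 1: gap with no exercise effect and no ceiling.** Take the norm at the 25th percentile, r = 0.8 and uncorrelated measures. The bivariate normal probability of being below the cut both times is 0.169.

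- Impaired at entry: share unimpaired at 12 weeks = 1 − 0.169/0.25 = 32%.
- Not impaired at entry: with no effect, 0.25 are below the cut at 12 weeks, of whom 0.25 − 0.169 = 0.081 come from this group. Share unimpaired = 1 − 0.081/0.75 = 89%.
- Gap = 32 − 89 = −57 points.

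A simulation of 2,000,000 people with the entry rule applied gives the same values. Its zero-effect gaps, in points (impaired minus not impaired), are:

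| r | 25th pct, corr. 0 | 25th pct, corr. 0.3 | 50th pct, corr. 0 | 50th pct, corr. 0.3 |
|---|---|---|---|---|
| 0.7 | −47 | −43 | −49 | −42 |
| 0.8 | −57 | −53 | −57 | −49 |
| 0.9 | −70 | −67 | −64 | −56 |
| 0.95 | −79 | −76 | −66 | −57 |

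The range is −42 to −79.

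**Step 2: does the gap respond to the exercise effect?** With r = 0.8, the 25th-percentile norm and uncorrelated measures:

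| Effect in impaired group (SD) | Gap (points) |
|---|---|
| 0 | −57 |
| 0.5 | −29 |
| 1.0 | −7 |
| 1.5 | +5 |

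It does, so entry status dominates the result but does not determine it.

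**Step 3: does the gap respond to a ceiling?** Let Y be the uncapped value, c the cap and k the norm, with c ≥ k. Then min(Y, c) ≥ k exactly when Y ≥ k, so neither percentage changes. In the simulation, capping at the 75th percentile left the gap identical in every scenario. For timed balance, the highest Table 1 threshold is 8 seconds against a cap of 30. Only a norm near 30 seconds would make the percentage an approximate count of people at the cap, and even then at 12 weeks and not at baseline.

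**Step 4: size of the bias in the primary comparison.** If a share p of the untargeted group is at the cap and the cap removes an average gain g from each, that group's mean change is lowered by p × g. The article gives neither p nor g, so no figure follows.

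**The case against.** The strongest defence is that the endpoint's indifference to a cap is a merit. Raw change is distorted by a ceiling; the share reaching normal values is not. Read that way, the analysis replaces change with attainment, which is a legitimate secondary question. This stands as a reason to keep the percentage. It does not rescue the stated purpose: the section says it is exploring how much improvement was possible, and comparing attainment between groups sorted by starting level does not show that.

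Three further points stand:

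- The cut-off is still to be derived. A reader might infer that the analysis says nothing at all about ceilings, but a norm close to the attainable maximum would carry some indirect information on headroom.
- A reader might infer that the result is fixed by selection. Step 2 contradicts this: the gap halves at a 0.5 SD effect and can reverse at 1.5 SD.
- The explicit maxima concern balance only. No scale limit is stated for strength or knee flexion. For the Four Balance Test Scale, a 0 to 5 range is given for four postures without saying which performance earns the top score.

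It is also fair that this is one exploratory analysis in an uncontrolled proof-of-principle study, and that the article openly acknowledges the unequal starting points.

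**Conclusion.** The concern holds in limited form. As described, the comparison is strongly confounded by entry status: a gap of roughly 40 to 80 points is expected with no exercise effect and no ceiling. That range rests on assumed normality, reliability of 0.7 to 0.95, and a norm at the 25th or 50th percentile. The insensitivity to a cap above the norm is algebra and needs none of those assumptions. Unless the norm is placed near the scale maximum, the analysis neither measures headroom nor shows what a ceiling does to the primary comparison.

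It would go too far to say that the primary balance result is inflated by a known amount. The direction is plausible, but the number of participants at either cap is not given. The consequence is for how the primary comparison is interpreted; the primary test itself is unaffected. This is more than missing detail, because the article specifies an analysis that does not answer the question it sets.

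**What to change.** For the two balance outcomes:

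1. Report, by targeted and untargeted group, the share at the maximum (30 seconds; top Four Balance Test Scale score) at the nurse baseline visit.
2. Repeat the primary change-score comparison excluding those participants, and present it beside the full result.

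If the 12-week percentage without impairment is kept, show it with the baseline percentage for both groups and describe it as attainment of normal values, not as a test of ceiling effects. Keep both groups in that table: in Step 1, 32% of impaired participants cross the cut with no exercise effect, so recovery in the targeted group alone would mislead.

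The cost is a change of wording, a baseline count and one extra run per balance outcome, all on measurements already planned. The downside is fewer comparison participants in the restricted run, from a total of 60, and so a wider interval. The restricted run addresses the ceiling only; it does not remove regression to the mean or the other differences between groups selected on baseline level.
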